#### Semi-structured individual interviews

We will conduct parent interviews to evaluate the fidelity to and appropriateness of implementation strategies 6 and 7, as well as the acceptability and feasibility of IV-to-oral switch therapy (online supplemental file 8). Starting 3 months after the implementation begins, parents of each neonate discharged on oral therapy at participating sites will be invited to participate by their paediatricians. The first parent couple(s) per site who agree will be contacted by the interviewer to schedule the interview 1–4 weeks after discharge. Data on parents’ gender, age and number of children will be recorded. We will also conduct individual interviews with maternity nurses to evaluate the fidelity to and appropriateness of implementation strategies 1 and 5, as well as the acceptability and feasibility of IV-to-oral switch therapy (online supplemental file 9). Due to the relatively rare occurrence of neonatal oral therapy cases in the routine practice of maternity nurses, local obstetric partnerships and parents with a neonate on oral therapy will be asked to help identify maternity nurses who have been involved in the care for neonates with oral therapy at home. Data on maternity nurses’ gender and years of working experience will be recorded. For both maternity nurses and parents, we aim to conduct 12 interviews or as many as necessary to achieve data saturation. Data saturation is defined as the point at which no new topics emerge across three consecutive interviews. For all interviews, a semi-structured interview guide will be used. All sessions will be audio-recorded, transcribed verbatim and securely stored on a departmental disk. Participant anonymity will be ensured by removing identifying information from the transcripts.

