#### Strategy 4: Nurse education leader and ready-to-use presentation template

Per site, one or more nurses will be appointed by the local implementation team as responsible for educating the nursing staff. These nurse education leaders will educate their peers on the antibiotic stewardship interventions through bedside teaching, conducting online or live educational sessions or providing an instructional email. A ready-to-use presentation will be available for the responsible nurses to use during education and to disseminate to all other nurses. All nurses are asked to sign off once they have received education on IV-to-oral switch therapy.

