#### Strategy 5: Facilitation of EOS calculator integration in the electronic health record

In hospitals using the HiX (Chipsoft) electronic health record (EHR), the EOS calculator will be integrated directly into the patient record, eliminating the need to access it externally. The central research team will coordinate with Chipsoft to ensure the availability of the HiX calculator at participating sites and will provide an instruction manual for actually activating and using the calculator in practice. In hospitals not using HiX, a link to both the Kaiser Permanente website and the published open-source version of the EOS calculator will be provided, ensuring hospitals are not dependent on logistical, technical or maintenance issues associated with the Kaiser Permanente website.^35 36^

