#### Strategy 6: Primary care maternity nurse knowledge module and newsletter

A targeted informative module on IV-to-oral switch therapy will be made available for all primary care maternity nurses on the National Knowledge Centre of Maternity Care’s website’s database (http://www.kckz.nl/), which is the formal website of Dutch maternity care guidelines. This module will cover general background information on EOS and IV-to-oral switch therapy, along with detailed information on care responsibilities, the instructions provided to parents regarding antibiotic administration, safety precautions and contact information. Additionally, this document, including further explanations, will be distributed to all maternity nurses through the KCZK’s email newsletter.

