#### Surveys

All paediatricians of the participating sites will be invited to complete a survey both before and 1 year after the active implementation period to assess changes in knowledge and practice gaps and the adoption of the interventions. Additionally, the post implementation survey will evaluate fidelity to and appropriateness of the implementation strategies 1–3 and 8 and assess acceptability and feasibility of the antibiotic stewardship interventions (onlinesupplemental files 4  5). Paediatric residents will only take part in the post implementation survey, as their frequent rotations across different workplaces make pre-implementation comparisons unfeasible. Neonatology nurses will also be invited to complete a survey, specifically to assess the acceptability and feasibility of IV-to-oral switch therapy and the fidelity to and appropriateness of strategies 1, 6 and 7 (online supplemental file 6). All surveys will be distributed via the Castor EDC system.

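### The strategy numbers assigned to surveys and interviews do not match the strategy list (5, 6 and 8 go to the wrong respondents), and no survey or interview covers strategy 4

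*Protocol article*

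**What the plan says.** The implementation strategies section of the protocol article numbers eight strategies:

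- 1: local implementation team
- 2: paediatric kick-off session
- 3: podcast series
- 4: "Strategy 4: Nurse education leader and ready-to-use presentation template"
- 5: "Strategy 5: Facilitation of EOS calculator integration in the electronic health record"
- 6: "Strategy 6: Primary care maternity nurse knowledge module and newsletter"
- 7: guided practice, leaflet and checklist for parents
- 8: instructional video for parents

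Two later sections assign strategies to respondents by these numbers.

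- Surveys, paediatricians and (post-implementation only) residents: "the post implementation survey will evaluate fidelity to and appropriateness of the implementation strategies 1–3 and 8".
- Surveys, neonatal nurses: "the fidelity to and appropriateness of strategies 1, 6 and 7".
- Semi-structured individual interviews, parents: "We will conduct parent interviews to evaluate the fidelity to and appropriateness of implementation strategies 6 and 7".
- Semi-structured individual interviews, maternity nurses: "maternity nurses to evaluate the fidelity to and appropriateness of implementation strategies 1 and 5".

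The sections on focus groups, logbook and field notes give no strategy numbers. Fidelity to the strategies and their appropriateness are secondary outcomes of the process evaluation.

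**The concern.** Appropriateness is a judgement that only people who met a strategy can make. If the assignments are followed as printed, home-care maternity nurses are asked about a hospital record tool and not about the module written for them. Parents are asked about a module for professionals and not about the video made for parents. Neonatal nurses are not asked about their own training. The protocol intends the process evaluation to show which strategies were relevant and to guide improvement, and it also promises practice and policy recommendations. A strategy rated by the wrong group, or by none, adds little to either, and a question left out of a survey or interview is hard to recover afterwards.

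**Working it through.** There is no figure to reproduce. The check is a cross-tabulation of the strategy list against the assignments, followed by a test of whether one renumbering explains the mismatch.

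**Step 1. As printed.** The users are taken from each strategy's own description. For strategy 5 they are inferred, because the text places the calculator in the hospital patient record without naming a profession.

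| Strategy | Users by its description | Asked, by the printed numbers | Fit |
|---|---|---|---|
| 1 Local team | Hospital staff and the surrounding care network | Paediatricians/residents, neonatal nurses, maternity nurses | Yes |
| 2 Kick-off session | Paediatricians, residents | Paediatricians/residents | Yes |
| 3 Podcast | Mainly paediatricians, residents | Paediatricians/residents | Yes |
| 4 Nurse education | Hospital nursing staff | None | Missing |
| 5 Calculator in record | Hospital clinicians (inferred) | Maternity nurses only | No |
| 6 Maternity nurse module | Maternity nurses | Neonatal nurses, parents | No |
| 7 Practice, leaflet, checklist | Parents, neonatal nurses | Neonatal nurses, parents | Yes |
| 8 Parent video | Mainly parents; also neonatal and maternity nurses | Paediatricians/residents only | No |

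For strategy 6 the target is explicit: the module "will be made available for all primary care maternity nurses". Result: 4 of 8 strategies fit (1, 2, 3, 7), 3 of 8 go only to groups not described as users (5, 6, 8), and 1 of 8 goes to no survey or interview (4).

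**Step 2. Does one move explain it?** Suppose the calculator strategy was number 8 when the two data-collection sections were written. Then 5 is the maternity nurse module, 6 is practice and leaflet, 7 is the video, and 1 to 4 are unchanged. The same printed numbers now read:

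| Respondents | Printed numbers | Meaning under the supposed order |
|---|---|---|
| Paediatricians/residents | 1–3, 8 | Team, kick-off, podcast, calculator |
| Neonatal nurses | 1, 6, 7 | Team, practice and leaflet, video |
| Parents | 6, 7 | Practice and leaflet, video |
| Maternity nurses | 1, 5 | Team, their own module |

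Every assignment fits its respondents. Number 4 still appears nowhere, so its absence is not part of the renumbering.

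**Step 3. What other sources hold on strategy 4.** The strategy 4 text asks nurses to sign off after education on oral switch therapy. That records receipt for one of the three interventions. The logbook tracks whether strategy components were carried out, and the field notes are organised by strategy. All of these can inform fidelity. They are nurses' confirmations or the central team's records, not recipients' judgements of appropriateness. The focus groups list paediatricians, residents and nurse practitioners, not neonatal nurses.

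**The case against.** The strongest reply is that for strategies 5, 6 and 8 this is a labelling slip. Nobody would choose to have maternity nurses rate a hospital record tool, and step 2 shows how the numbers could have arisen. The survey and interview guides are supplements that are not shown, and they may already ask the right people the right questions. This stands, and it limits what can be claimed for those three strategies to an inconsistency in the article.

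A reader might infer that nobody evaluates strategy 4, or that half of the strategies will yield no usable evidence. The documents support neither. Fidelity to strategy 4 can be recorded through the sign-off, logbook and field notes. The focus groups have no strategy restriction and include clinicians likely to use the calculator. The video is linked by a code on the leaflet in strategy 7, on which parents and neonatal nurses are asked, so their questions may reach it.

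These points do not remove the error. The article states the mapping explicitly, so this is not a detail lost in condensation, and anyone fielding or reporting from it would be misled. Nor does the reply supply a respondent group for the appropriateness of strategy 4.

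**Conclusion.** The point holds in two parts. First, the printed numbers contradict the strategy list for three of eight strategies (5, 6 and 8). Stale numbering is the likeliest cause; that is an inference from the pattern, since the documents do not state it. Whether any data are affected depends on instruments that are not shown. Second, one strategy of eight (4) is in no survey or interview under either numbering, and no respondent group is assigned to judge its appropriateness.

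The effect is confined to the process-evaluation outcomes, fidelity to and appropriateness of the strategies. The primary outcome, days on therapy, and the clinical secondary outcomes are untouched. The change should be made, because the error sits in an operative data-collection rule and is cheap to correct.

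**What to change.** Correct the numbers in the two data-collection sections to the current list:

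- Paediatricians and residents: 1–3 and 5.
- Neonatal nurses: 1, 7 and 8, plus 4.
- Parents: 7 and 8.
- Maternity nurses: 1 and 6. Strategy 1 should stay with them, because the protocol assigns it and the local team's task extends to the neonatal care network.

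Then check each survey and interview guide against this mapping. If the neonatal nurse survey has no items on strategy 4, add them.

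The cost is a text correction in two sections, a check of the guides, and possibly a few extra survey items. Those items would be a small amount of new data collection. The study period runs to June 2026, the article appeared in November 2025, and parent interviews begin three months after implementation starts, so some may already have been held. Those cannot be changed. If their guide followed the printed numbers, the report should say which strategies those respondents were asked about.

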#### Logbook

During the implementation phase and its preparation, the central research team will maintain a site-specific logbook to systematically document all implementation activities. This will include recording the completion dates of tasks assigned to local champions, verifying and updating local protocols and tracking the execution of implementation strategy components, such as distributing printed materials or uploading documents. Any ad hoc changes to the implementation strategies or adaptations to the interventions will also be logged. Data for the logbook will be collected from various sources, including site visits, email correspondence, phone calls and meetings with local implementation teams and other relevant stakeholders.

#### Field notes

During the implementation phase and its preparation, the central research team will maintain detailed field notes to document site-specific observations. These notes will capture information on implementation factors, how barriers were addressed and suggestions for future improvements. The primary sources of data for the field notes will include site visits, emails, phone calls, meetings with local implementation teams and interactions with other stakeholders. Data from the field notes will be systematically organised using a matrix based on the implementation strategies and antibiotic stewardship interventions.

### Analysis

#### Primary outcome

An ITS analysis will be conducted to compare trend of overall DOT (all types of antibiotic agents) per 1000 live births pre- and post-intervention. The ITS will have at least four data points in the pre-implementation period and four datapoints in the post implementation period, based on quarterly intervals. If the number of cases allows dividing the data into more datapoints, this may be considered. To account for potential clustering of observations within hospitals and potential differences between hospitals, we will apply a mixed-effects segmented regression analysis for ITS (‘joinpoint regression’) with DOT as dependent variable and random intercept for each hospital. Also, we will include random slopes for the post-intervention trend, allowing hospitals to differ not only in baseline DOT levels but also in how they respond to the implementation. Fixed effects include intervention phase (pre/post) and segmented time after the intervention to estimate both immediate level changes and changes in trend. Confounders, including the number of positive blood cultures, mean gestational age and mean birth weight will be included as time-varying covariates. Depending on data availability, we may also examine trends during the intermediate implementation phase to explore changes during this transition period as secondary analysis. Autocorrelation of residuals will be checked by using the Durbin-Watson test, and if present, corrected. Results will be reported as adjusted changes in level and trend, with 95%CIs, reflecting both pooled effects and between-hospital variability. Additionally, a before-after comparison will be performed using a t-test or Mann-Whitney U test, for both overall DOT and DOT per individual antibiotic agent.

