**Methods and analysis:**

We will conduct a multicentre, prospective implementation study with interrupted time series and before-after analyses at the paediatric or specialised neonatal departments of 11 Dutch secondary hospitals and their surrounding neonatal care networks. A multimodal implementation strategy, designed using Implementation Mapping, is employed to facilitate implementation. The study population is twofold: (1) neonates born at 34 weeks of gestation or later with suspected EOS that will receive intervention-related care and (2) paediatricians, paediatric residents, neonatal nurses, maternity nurses and parents who are the focus of the implementation strategies. The primary outcome is days of antibiotic therapy per 1000 live-born neonates, which will be evaluated using interrupted time series analysis as well as before-after comparison. Secondary clinical outcomes will be assessed by comparing clinical data from the 12 months pre-implementation and post implementation. Implementation outcomes are adoption, fidelity, feasibility and acceptability of the interventions and fidelity and appropriateness of the implementation strategies. Implementation outcomes will be assessed using both qualitative and quantitative methods, including surveys, individual interviews and focus group interviews. A mixed-methods approach will be used to integrate clinical and implementation outcomes.

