However, all aforementioned interventions are not yet integrated into the Dutch national guideline on EOS management, which was most recently revised in 2017.^21^ Some Dutch hospitals already adopted one or more of the antibiotic stewardship interventions independently, but they are not applied in the vast majority. To integrate novel evidence into daily practice, active implementation should take place that carefully considers determinants influencing its application, including perspectives of all stakeholders.^22 23^ One of the challenges in the transition from evidence to practice is that most clinical interventions are researched primarily in controlled settings, yielding type 1 and 2 evidence on disease aetiology, burden and intervention effectiveness. As a result, there is limited type 3 evidence on how these interventions function in real-world environments, making it unclear what should be targeted for effective implementation.^24^ Moreover, since interventions are usually studied individually, little is known about how they interact with other evidence-based approaches for the same disease. Regarding neonatal antibiotic stewardship, several studies have reported the effect of implementing antibiotic stewardship interventions, yet reported mainly the impact on antibiotic prescription rates rather than data on the implementation context and strategies.^25 26^ The few studies that did emphasise implementation strategies were conducted at neonatal intensive care units with Level IV facilities.^27 28^ In contrast, most Dutch late preterm and term neonates at increased risk of EOS are born and treated in secondary hospitals (Level I–II facilities) and receive care in collaboration with the obstetric department and primary neonatal care.

Therefore, the primary aim of this study is to assess the impact of the strategy to implement an antibiotic stewardship bundle (the EOS calculator, PCT-guided therapy and IV-to-oral switch therapy) on antibiotic exposure for EOS in Dutch secondary hospitals. Secondary aims are to assess additional clinical outcomes and implementation outcomes, including the acceptability, feasibility and fidelity of the interventions, as well as the appropriateness of the implementation strategies.

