#### IV-to-oral switch therapy

IV-to-oral switch therapy applies to neonates born at 34 weeks or later, with a birth weight of >2000 grams, who are still suspected of infection, despite a negative blood culture, based on clinical symptoms/risk factors and abnormal infection parameters at the discretion of the paediatrician. After 36 hours of intravenous antibiotic therapy, if the neonate tolerates oral (tube) feeding and is clinically well, treatment is switched to oral antibiotic therapy with amoxicillin suspension. The recommended daily dose will be according to the Dutch Paediatric Formulary, 60 mg/kg/day in two doses, based on recently published data.^31^ In case the neonate vomits within half an hour of ingestion, administration should be repeated. The first dose will always be administered in the hospital, to assess tolerance by the neonate and educate parents. Afterwards, the location of treatment will shift from the hospital to the home environment in case this is considered safe. The paediatrician will stay responsible for neonatal care during the entire treatment period; care will not formally be transitioned to primary care. Nevertheless, informing primary care professionals about antibiotic treatment of the neonate is an essential part of the discharge procedure, as they are often a first contact person for families in the maternity period.

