#### Primary outcome

The primary outcome of this study is the total exposure to antibiotic therapy that was initiated within the first 72 hours after birth for the treatment of EOS. The exposure is measured in days on therapy (DOT), where a therapy day is defined as any calendar day when at least one dose of any antibiotic is administered. Besides the days on any antibiotic, also DOT per individual antibiotic agent (type and administration route) will be measured.

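### The only trend- and hospital-adjusted analysis is on overall DOT, which does not register intravenous days replaced by oral days; route-specific DOT gets only a crude before-after test

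*Protocol article*

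**What the plan says.** The Introduction of the protocol article sets the primary aim, which is to "assess the impact of the strategy to implement an antibiotic stewardship bundle (the EOS calculator, PCT-guided therapy and IV-to-oral switch therapy"; the effect of interest is on antibiotic exposure for early-onset sepsis.

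Under Study outcomes, Primary outcome, exposure is counted in days on therapy (DOT): "a therapy day is defined as any calendar day when at least one dose of any antibiotic is administered". The same section adds that "also DOT per individual antibiotic agent (type and administration route) will be measured", so DOT by route belongs to the primary outcome.

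Under Analysis, Primary outcome, the mixed-effects segmented regression is assigned to one series. It will "compare trend of overall DOT (all types of antibiotic agents) per 1000 live births pre- and post-intervention", with a random intercept per hospital and random slopes for the post-intervention trend. The section ends with a second analysis: "a before-after comparison will be performed using a t-test or Mann-Whitney U test, for both overall DOT and DOT per individual antibiotic agent". The abstract agrees that the primary outcome is one "which will be evaluated using interrupted time series analysis as well as before-after comparison".

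The section IV-to-oral switch therapy covers neonates who are still suspected of infection despite a negative culture. "After 36 hours of intravenous antibiotic therapy", and if feeding and clinical condition allow, "treatment is switched to oral antibiotic therapy with amoxicillin suspension". It states no total course length for switched neonates.

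**The concern.** The switch changes the route of a treatment day and does not by itself remove the day. Under the day count above, an IV day that becomes an oral day still adds one to overall DOT. However well the switch is taken up, the ITS on overall DOT will not show it unless total course length changes as well.

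Route-specific DOT, which would show it, gets only a two-group test. That test does not model the pre-existing trend or the clustering within hospitals, which the protocol gives as its reason for using a mixed model on overall DOT. The analysis section also speaks of DOT per agent without repeating the route qualifier from the outcome definition. Read literally, IV and oral use of the same agent could be merged.

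This matters for the hospital-level results. Strategy 1 supplies the intervention protocols as separate modules that a site can adopt independently. A site whose main change is the switch would show a flat overall DOT. The random slopes, presented as how hospitals respond to the implementation, would then partly reflect which modules were adopted.

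**Working it through.** **Inputs.** From Sample size: 38 treated neonates per 1000 live births, 68.5% treated for 2 days and 31.5% for 7 days. From IV-to-oral switch therapy: the switch follows 36 hours of IV treatment, which touches 2 or 3 calendar days depending on the time of the first dose. Assumptions made here: the total course stays at 7 days, there is no oral use before implementation, and a day with both routes counts once, as IV.

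**Step 1: the protocol's own baseline.**
- Short courses: 0.685 × 38 × 2 = 52.06
- Full courses: 0.315 × 38 = 11.97 neonates; × 7 = 83.79
- Total: 135.85, which reproduces the stated 136 DOT per 1000.

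**Step 2: switch every full course and change nothing else.**

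| | Before | Switch after 2 IV days | Switch after 3 IV days |
|---|---|---|---|
| IV DOT | 135.85 | 52.06 + 11.97 × 2 = 76.00 | 52.06 + 11.97 × 3 = 87.97 |
| Oral DOT | 0 | 11.97 × 5 = 59.85 | 11.97 × 4 = 47.88 |
| Overall DOT | 135.85 | 135.85 | 135.85 |
| Change in IV DOT | – | −44.1% | −35.2% |
| Change in overall DOT | – | 0% | 0% |

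**Step 3: partial uptake.** If a quarter of full courses are switched, IV DOT falls by 0.25 × 59.85 = 14.96 (11.0%) or 0.25 × 47.88 = 11.97 (8.8%). Overall DOT again changes by 0.

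**Step 4: dependence on course length.** The zero holds only if the course length is unchanged. Overall DOT is 52.06 + 11.97 × L, where L is the length of a full course in days:
- L = 5: 111.91 (−17.6%)
- L = 6: 123.88 (−8.8%)
- L = 7: 135.85 (0%)
- L = 8: 147.82 (+8.8%)

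**Step 5: the other components, with no switch.** Take 20 starts per 1000 and a full-course share halved to 15.75%. Overall DOT is 20 × (0.8425 × 2 + 0.1575 × 7) = 55.75, near the stated goal of 60. Without a switch all of it is IV, so IV DOT also falls from 135.85 to 55.75. Only 20 × 0.1575 = 3.15 full courses per 1000 then remain. Switching all of them would move 3.15 × 5 = 15.75 or 3.15 × 4 = 12.6 days from IV to oral.

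Step 2 is therefore an upper bound. Step 5 shows that IV DOT responds to all three components.

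**The case against.** A reader might infer that full success of the switch would show as no effect anywhere in the primary analysis. The documents do not support that. DOT by agent and route is part of the primary outcome, and DOT per agent is tested before-after under the same heading. If split by route, that test would show the fall in IV days and the new oral days. What it lacks is adjustment for trend and hospital.

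A reader might also infer that overall DOT is the wrong primary outcome. It is not. The aim is antibiotic exposure under the bundle as a whole, and an oral day is exposure. The goal of 60 DOT per 1000 rests on fewer starts and fewer full courses, and the switch is not named in it.

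The switch is also recorded elsewhere: adoption by department, fidelity among eligible patients, proportion switched and duration of hospital stay. These data can help explain a site with flat overall DOT. However, the clinical outcomes among them are again compared only before and after, by two-group tests.

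Two further points stand. To say that the switch cannot lower overall DOT is too strong, because no total course length is given for switched neonates. And IV DOT cannot by itself judge the switch, since it also falls when fewer courses start or when treatment stops earlier.

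Finally, an additional secondary model could be left to a fuller analysis plan. But the article does not leave this open: it assigns the ITS to overall DOT and the two-group test to DOT per agent.

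**Conclusion.** The point holds as a design weakness, not as a contradiction. With an unchanged total course, the only analysis that adjusts for trend and hospital is insensitive to one of the three bundle components. It is not void for the bundle. Overall DOT remains valid for total exposure, and the other two components can move it substantially.

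On the protocol's inputs, the shift that the ITS could miss is at most 48 to 60 IV days per 1000 live births (35% to 44% of IV DOT). This assumes that every full course is switched, that full courses stay at 7 days and that there was no earlier oral use. The real shift would be smaller. Eligibility is limited by culture result, birth weight, feeding and clinical condition, and the other components reduce the number of full courses. At about the study's own target it is roughly 13 to 16 days per 1000. These falls should not be judged against the 10% relevance threshold, which was set for total DOT.

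**What to change.** Keep overall DOT as the primary outcome and make four additions before results are seen:

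1. As a prespecified secondary analysis, fit the same mixed-effects ITS to IV DOT per 1000 live births and report oral DOT beside it. Count a day with both routes once, as IV.
2. Write the split by administration route into the Analysis section for the before-after comparison, to match the outcome definition. Confirm that the automated extraction delivers route by date; the listed data items name agents, dosages and duration but not route.
3. State that overall DOT does not measure the switch.
4. State that IV DOT reflects all three components, so the switch is read from IV and oral DOT together with the proportion switched and site-level adoption. Use the adoption data when interpreting the hospital-specific slopes.

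The cost is one more secondary model and one more comparison to report, on an outcome that the protocol already plans to measure.

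### If hospitals share irregular quarterly fluctuations, the hospital-only random effects in the primary ITS model make the intervals for level and trend change too narrow

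*Protocol article*

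**What the plan says.** The protocol article, Analysis – Primary outcome, sets out the random part of the model. It has the outcome "with DOT as dependent variable and random intercept for each hospital", and then "we will include random slopes for the post-intervention trend, allowing hospitals to differ not only in baseline DOT levels". The stated reason is "To account for potential clustering of observations within hospitals and potential differences between hospitals". On the fixed side, "Fixed effects include intervention phase (pre/post) and segmented time after the intervention", with covariates "including the number of positive blood cultures, mean gestational age and mean birth weight will be included as time-varying covariates". The series has "at least four data points in the pre-implementation period and four datapoints in the post implementation period, based on quarterly intervals", and on a finer division the text says "If the number of cases allows dividing the data into more datapoints, this may be considered".

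The only dependence check named is Durbin-Watson on the residuals, with correction if needed. Results are to be given as adjusted level and trend changes with 95% CIs.

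Study design gives every site the same 2023 baseline year. It places 9 months of implementation and 12 months of post-implementation follow-up in a window from January 2024 to June 2026.

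**The concern.** Level change and trend change are contrasts over calendar time, and there is no control series. Both random terms are indexed by hospital. The intercept absorbs stable differences between hospitals, and the slope absorbs differences in how they respond. Neither can absorb a quarter in which all hospitals are high or low together. That movement goes into the residual, where the model treats it as independent across hospitals and averages it over 11. More hospitals do not reduce a shared error, but the model's standard error assumes that they do.

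This differs from correlation over time within a hospital, which is what Durbin-Watson addresses, and from a fixed seasonal pattern. At stake is whether one or two shared low quarters could be reported as an effect of the implementation strategy with a confidence interval that excludes zero.

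**Working it through.** **1. Baseline from the plan's own figures (Sample size).** 0.685 × 38 × 2 + 0.315 × 38 × 7 = 52.06 + 83.79 = 135.85, which reproduces the stated 136 DOT per 1000. The stated total of 2790 is for a two-group comparison and does not enter here.

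**2. Independent noise per hospital-quarter.** From the same mix, the variance per birth is 0.038 × (0.685 × 4 + 0.315 × 49) − 0.13585² = 0.69065 − 0.01846 = 0.6722, so the SD is 0.82 day. An average of 2500 births a year is 625 a quarter: 1000 × 0.82 / √625 = 32.8 DOT per 1000.

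**3. Formula for the understatement.** Let s be the shared quarterly SD. The pooled quarterly mean of 11 hospitals has variance 32.8²/11 + s², while the model credits it with roughly 32.8²/11. The ratio of true to reported SE is therefore about √(1 + 11s²/32.8²). For s = 3.4, 6.8, 13.6 and 20.4 (2.5%, 5%, 10% and 15% of 136) this gives 1.06, 1.21, 1.70 and 2.29. Since 32.8/√11 = 9.9, a shared SD of 9.9 (about 7% of baseline) already equals all the independent noise left in the pooled mean.

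**4. Simulation with no true effect.** Settings: 11 hospitals, 4 + 4 quarters, a common 9-month gap, a REML fit with random hospital intercept and random post-slope, and fixed phase and post-time. Assumed values: hospital intercept SD 30, post-slope SD 5 per quarter, Gaussian errors, 600 runs per row. The three planned covariates were not simulated. The comparator is a regression on the 8 pooled quarterly means with a t reference.

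| Shared SD (% of 136) | True SD / mean model SE (level, trend) | Type I error, planned structure (level, trend) | Type I error, quarter-level (level, trend) |
|---|---|---|---|
| 0 | 1.00, 0.97 | 5.3%, 4.8% | 4.8%, 5.7% |
| 5% | 1.17, 1.17 | 10.5%, 9.0% | 4.0%, 4.0% |
| 10% | 1.63, 1.65 | 22.5%, 23.3% | 6.0%, 7.2% |
| 15% | 2.05, 1.94 | 35.3%, 31.2% | 4.8%, 5.0% |

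The simulated ratios fall a little below the formula at large s because the shock also raises the estimated residual variance. At 10% the model reports a mean SE of 10.1 for level change against a true SD of 16.5. The reported 95% half-width is thus about 1.96 × 10.1 = 19.8, where 1.96 × 16.5 = 32.3 would be needed. The reduction that the plan calls clinically relevant is 135 − 121.5 = 13.5.

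A larger simulation (8,000 runs per setting) gave level-change rejection of 5.1%, 6.4%, 9.7%, 15.4% and 21.5% at s = 0, 3.4, 6.8, 10 and 13.6. With a baseline trend added the rates were 5.0%, 6.6%, 10.4%, 15.6% and 22.5%. Period-level error gave 4.6–5.5% throughout.

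**5. Would Durbin-Watson flag it?** The average statistic stayed between 1.99 and 2.15 in every common-start setting, so no.

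**6. Staggered starts.** With sites starting over four successive quarters, type I error (level, trend) is 7.3% and 6.3% at a 5% shared SD, and 15.7% and 8.8% at 10%.

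**7. Monthly intervals.** With shocks independent from month to month, the hospital-only model still rejects 6.6% at s = 6.8 and 11.8% at 13.6, against 5.1% with month-level error. If a shock lasts a whole quarter, independent month-level error on 12 + 12 months rejects about 8.5–8.6%, 11.5–12% and 15–16% at s = 6.8, 10 and 13.6.

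**The case against.** - **The shared fluctuation is assumed.** A reader might infer that the planned intervals are certainly too narrow. The documents do not support that. They give no figure for shared movement, and at zero the planned model is calibrated. This stands, and the point is therefore conditional.
- **A common calendar is not documented.** A reader might also infer that phase and time are identical at every site, so that the effect is wholly confounded with calendar quarter. Only the 2023 baseline is stated as common. The study periods from January 2024 take 9 + 12 = 21 months of a 30-month window, which leaves room for staggered starts, and the logbook records completion dates by site. Staggering shrinks the problem, mainly for trend, but does not remove it.
- **The planned covariates were not simulated.** Positive cultures, gestational age and birth weight may absorb part of a shared shock. Hospital-specific noise above 32.8 would also reduce the inflation. Both affect size.
- **Some of this belongs in an SAP.** A choice between degrees-of-freedom approximations does, and its absence is no finding. The random-effects structure, however, is stated in the article, and an analyst following it would fit the model examined here.
- **Monthly data should not be imposed.** At 3.8% initiation, a 1000-birth hospital has 38/12, about 3 treated neonates a month, and 20/12, under 2, at the 2% goal. The plan's condition on case numbers is sensible. Step 7 also shows that monthly intervals alone are no cure.
- **Consequences are bounded.** The article already says that lack of randomisation limits causal conclusions. A fall from 136 to 60, if it appeared as a level change, would be 76/16.5 = 4.6 true SDs even at a 10% shared SD. The risk concerns small effects such as the 10% reduction.

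**Conclusion.** The concern holds in conditional form. The stated model has no calendar-period term, so if hospitals share irregular quarterly fluctuations, the SEs and CIs for the pooled level and trend change are too small and the planned residual check will not show it.

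Under 4 + 4 quarters, a common start, 625 births per hospital-quarter and no covariate adjustment, type I error for level change is about 5% at shared SD 0, 6–7% at 2.5% of baseline, 10% at 5% and 22–23% at 10%. Trend change behaves much the same. Staggered starts or effective covariates make it smaller. Which of these values applies cannot be settled from the documents.

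**What to change.** Add a random effect for calendar period crossed with hospital, indexed by calendar quarter and not by time since a site's own start. Base the tests and CIs for level and trend change on period-level degrees of freedom. With 8 common quarters these are 8 − 3 = 5 for intercept, phase and post-time, or 4 if a baseline trend is added. Alternatively, report a period-level analysis of the pooled series alongside the planned model. State the site start dates, since the size of the problem depends on them.

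Finer intervals can be used where case counts allow, as the plan already says, but only together with the period effect and with serial correlation in that effect handled.

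The cost is one variance term and no new data. Intervals will be wider, clearly so if only 8 quarters are used. If there is no shared fluctuation, the estimated period variance should be near zero.
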